## Methods/design

### Study design

GARFIELD in the UK is primary care based and aims to recruit 4,582 patients at more than 100 sites across the UK. Enrolment will take place in five independent sequential cohorts, parallel to the global study. Similar to the global study, Cohort 1 will include a retrospective validation cohort of patients diagnosed with AF between 6 months and 24 months previously. Data will be extracted through a case notes review at baseline, and at every 4 months until 24 months after diagnosis. The data will be collected using an electronic case report form (eCRF). A summary of the UK study design is provided in Figure 2.

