### Study setting

In the UK, all healthcare delivery is centred on the general practitioner (GP), with referrals for specialists and for routine admission to hospital organized at the GP level. As a result of the National Health Service structure, GPs maintain in their surgeries a complete medical history of their patients. Recruiting from the general practices will therefore capture all patients diagnosed with AF regardless of their care settings, and in the UK, these include hospital departments (cardiology) and emergency settings. The UK is therefore recruiting solely from the primary care setting; nevertheless, we expect to achieve a representative sample of patients with AF being cared for in the UK, comparable to the sample recruited in the global study.

Investigator sites (GP practices) will be representative of the UK, and will include sites in England, Wales, Scotland, and Northern Ireland, with the aim of achieving a sample representative of the geographical distribution of the UK population. Practices will be recruited and trained in collaboration with national research networks. The Primary Care Research Network (PCRN) England provides a world-class infrastructure to conduct clinical research in primary care settings in the NHS by supporting and facilitating recruitment and set up of sites. PCRN England is delivered through eight local research networks that cover the whole of England. Similar networks operate in Scotland (Scottish PCRN), Northern Ireland (Northern Ireland Clinical Research Network), and Wales (National Institute for Social Care and Health Research). Expressions of interest will be sent to practices by the research network for each region, and sites will be selected from the responses received.

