### Sample size and data analysis

The total projected sample size for the UK is 4,582, comprising 417 retrospective patients for Cohort 1 and 833 prospective patients for Cohorts 1 to 5. With these projected sample sizes the precision of estimated incidence of stroke is set out in Table 1 for different levels of incidence.

**Table 1 T1:** Precision of estimated incidence of stroke for different levels of incidence, and confidence intervals on effect sizes for quantitative measures

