	**Width of 95% confidence interval**		
**Expected incidence of stroke**	**Sample size of retrospective patients: 417**	**Cohort size of prospective patients: 833**	**Total sample size of 4,582**
2.5%	±1.5%	±1.1%	±0.5%
5%	±2.1%	±1.5%	±0.6%
10%	±2.9%	±2.0%	±0.9%
20%	±3.8%	±2.7%	±1.2%
30%	±4.4%	±3.1%	±1.3%
40%	±4.7%	±3.3%	±1.4%
50%	±4.8%	±3.4%	±1.4%
Width of 95% confidence interval			
Sample size of retrospective patients: 417		Cohort size of prospective patients: 833	Total sample size of 4,582
0.14		0.10	0.04

An interim analysis will be done at the UK level for the baseline data in each cohort and after all patients in each of the first four cohorts have completed the study. For a full analysis, baseline data, follow-up data, and study endpoint data will be summarised overall and by treatment groups, cohort, and region. Summaries of categorical data will be presented as frequency counts, percentages, and 95% confidence intervals. Continuous data will be presented as means (standard deviations), medians (with 95% confidence intervals), interquartile ranges, minimum, maximum, and number of patients.

Comparison of follow-up and outcome data between treatment groups, cohorts, and regions will be made using linear (for continuous outcomes) or non-linear (for categorical outcomes) mixed modelling with practice included as a random effect. Association between outcome variables and baseline data will be explored using the same method. For continuous data, normality of residuals will be tested using the Kolmogorov–Smirnov test and transformation or bootstrapping will be implemented where required. Time-to-event analysis will use Kaplan–Meier and Cox regression analyses to summarise and explore the association with baseline and other pertinent data. Comparison of CHADS_2_, CHA_2_DS_2_VASc, and HAS-BLED risk measures will be compared on the basis of receiver-operating characteristic curve analyses. The baseline characteristics of the patients – who have been classified as at risk of stroke according to physician-perceived risk factors or combinations of factors – will be reported.

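### Table 1 projects precision as if patients were independent, although they are recruited within GP practices; the pooled 4,582 column is too favourable if there is any within-practice correlation

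*Protocol article*

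**What the plan says.** Under Study design, the article says that the UK study "aims to recruit 4,582 patients at more than 100 sites across the UK". Study setting identifies those sites: "Investigator sites (GP practices) will be representative of the UK".

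Under Sample size and data analysis, the 4,582 is described as "comprising 417 retrospective patients for Cohort 1 and 833 prospective patients for Cohorts 1 to 5". The section continues: "With these projected sample sizes the precision of estimated incidence of stroke is set out in Table 1 for different levels of incidence". Table 1 then gives ± half-widths under the label "Width of 95% confidence interval" for 417, 833 and 4,582 patients, at incidences from 2.5% to 50%. It mentions no design effect, ICC or clustering.

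Further on, the same section plans comparisons between treatment groups, cohorts and regions by "mixed modelling with practice included as a random effect", and uses the same method for associations with baseline data. For descriptive results it says only: "Summaries of categorical data will be presented as frequency counts, percentages, and 95% confidence intervals". It does not say how those intervals will be calculated.

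**The concern.** The sampling runs through practices, and the analysis section treats practice as a source of correlation when groups are compared. The precision that accompanies the sample size sets that correlation to zero. The two parts of one section therefore rest on different assumptions about the same data. This is a printed figure that does not match the design, so it differs from a detail that the article could leave to a later document.

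The registry is largely descriptive, so interval estimates are among its main products. Clustering is most plausible for percentages that depend on the practice's clinicians, such as the decision to anticoagulate, which is among the UK aims. It is probably weaker for stroke, the outcome for which Table 1 is labelled. The pooled column makes the most precise claim and is the most exposed, because it has the most patients per practice.

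**Working it through.** **Inputs from the article.** n = 417, 833 and 4,582 (417 + 5 × 833 = 4,582); more than 100 practices; 95% two-sided intervals.

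**Assumed inputs.** The ICC, for which the article gives no value; practices of equal size; every practice contributing to every cohort.

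**Step 1: reproduce Table 1.** The simple-random-sample half-width is 1.96 × √(p(1 − p)/n). For n = 4,582 and p = 0.05 it is 1.96 × √(0.05 × 0.95/4,582) = 0.631%, printed as ±0.6%.

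| Incidence | n = 417: computed (printed) | n = 833: computed (printed) | n = 4,582: computed (printed) |
|---|---|---|---|
| 2.5% | 1.498 (1.5) | 1.060 (1.1) | 0.452 (0.5) |
| 5% | 2.092 (2.1) | 1.480 (1.5) | 0.631 (0.6) |
| 10% | 2.879 (2.9) | 2.037 (2.0) | 0.869 (0.9) |
| 20% | 3.839 (3.8) | 2.716 (2.7) | 1.158 (1.2) |
| 30% | 4.398 (4.4) | 3.112 (3.1) | 1.327 (1.3) |
| 40% | 4.702 (4.7) | 3.327 (3.3) | 1.418 (1.4) |
| 50% | 4.799 (4.8) | 3.395 (3.4) | 1.448 (1.4) |

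All 21 cells agree to the printed decimal. The effect-size row (0.14, 0.10, 0.04) matches 1.96 × √(2/n) = 0.136, 0.096, 0.041, which again contains no allowance for clustering.

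**Step 2: patients per practice.** With 100 practices, m = 4,582/100 = 45.8 in the pooled sample. Because the article says more than 100, this is an upper bound on the pooled average. For single cohorts, m = 417/100 = 4.2 and 833/100 = 8.3.

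**Step 3: design effect.** DE = 1 + (m − 1) × ICC, and the half-width is multiplied by √DE. For the pooled sample at ICC 0.01, DE = 1 + 44.82 × 0.01 = 1.45, and 0.631% × √1.448 = 0.76%. The last column is the coverage that a nominal 95% interval would have if it ignored clustering, 2Φ(1.96/√DE) − 1.

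| ICC (assumed) | DE, n = 4,582 | Half-width at 5% | Half-width at 50% | Coverage if clustering ignored |
|---|---|---|---|---|
| 0 (as printed) | 1.00 | ±0.63% | ±1.45% | 95% |
| 0.001 | 1.04 | ±0.65% | ±1.48% | 94.5% |
| 0.005 | 1.22 | ±0.70% | ±1.60% | 92.4% |
| 0.01 | 1.45 | ±0.76% | ±1.74% | 89.7% |
| 0.02 | 1.90 | ±0.87% | ±1.99% | 84.5% |
| 0.05 | 3.24 | ±1.14% | ±2.61% | 72.4% |

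The effective sample size is 4,582/1.448 = about 3,164 at ICC 0.01, and 4,582/3.241 = about 1,414 at ICC 0.05.

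**Step 4: sensitivity to the number of practices.** With 150 practices, m = 30.5. The pooled DE is then 1.30 at ICC 0.01 (±0.72% at 5% incidence) and 2.48 at ICC 0.05 (±0.99%).

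**Step 5: the smaller columns.** At ICC 0.01 and 100 practices, DE is 1.03 for 417 and 1.07 for 833. The 5% entries become ±2.12% and ±1.53%, which still print as ±2.1% and ±1.5%. At ICC 0.05, DE is 1.16 and 1.37, giving ±2.25% and ±1.73%.

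**The case against.** **Nothing in Table 1 is miscalculated.** The cells are correct for the formula used. This stands: the fault lies in the independence assumption, not in the arithmetic.

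**The size is assumed.** The article gives no ICC, and Table 1 concerns stroke, for which a low value is plausible. At ICC 0.001 the pooled 5% entry is 0.645% and would still print as ±0.6%. The large changes need an ICC near 0.05, which is easier to imagine for prescribing, and Table 1 makes no precision claim for prescribing. This also stands and limits the point. The pooled average of 45.8 per practice is an upper bound, so more practices would shrink the effect. Unequal practice sizes would raise it.

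**No stated criterion is missed.** The article sets no target precision, and its comparison and association models already include practice. True, but the printed precision is still offered as what the sample will deliver.

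**A reader might infer that the planned descriptive intervals will under-cover.** The article does not support that. It names no method for those intervals, a planning table does not fix how final results are computed, and the method may sit in an analysis plan that is not shown. The coverage figures above are therefore conditional on intervals computed as in Table 1. A reader might also take the whole table to be materially wrong. At ICC 0.01 the two smaller columns do not bear that out.

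**Conclusion.** The point holds for Table 1. Its precision assumes independent patients, which fits neither recruitment by practice nor the practice random effect in the same section. Any positive ICC makes the stated precision too favourable. The consequence falls mainly on the pooled column: at 5% incidence the factor √DE is 1.02 at ICC 0.001, 1.20 at ICC 0.01 and 1.80 at ICC 0.05, with 100 equal practices. For stroke the true loss may be small; for practice-driven percentages it could be substantial. These sizes depend on the assumed ICC, on the number of practices and on equal practice sizes. The single-cohort results also assume that all practices contribute to each cohort. Under-coverage of the descriptive intervals is a conditional risk, not an error shown in the article.

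**What to change.** Restate Table 1 with a design effect of 1 + (m − 1) × ICC for two or three labelled ICC values, and state the assumed number of practices. Use low values for stroke, and add higher ones if the table is also meant to support treatment proportions. Say that the descriptive 95% intervals for percentages use practice-clustered variance (for example a cluster-robust variance or a bootstrap of practices), so that they agree with the planned models. If the analysis plan already says this, a cross-reference is enough.

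The cost is a recomputed table and one sentence. The stated precision becomes slightly less favourable. Recruitment and data collection do not change.

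### Table 1's effect-size row appears to treat each column size as a per-group size, so the 0.04 given for the whole registry cannot be reached by a comparison within it

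*Protocol article*

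**What the plan says.** The point is confined to Table 1 of the Protocol article, under Sample size and data analysis. The text there fixes the UK sample, in a sentence that runs on to Cohort 5: "The total projected sample size for the UK is 4,582, comprising 417 retrospective patients for Cohort 1 and 833 prospective patients for Cohorts 1 to". The 833 is therefore per cohort, and 4,582 is everyone.

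The table has two blocks with the same three columns: "Sample size of retrospective patients: 417", "Cohort size of prospective patients: 833" and "Total sample size of 4,582". The upper block gives the precision of stroke incidence at seven assumed levels, each cell with a ± sign. The lower block is one row, 0.14 / 0.10 / 0.04, without ± signs. Both blocks are headed "Width of 95% confidence interval". Only the caption, in its second half, says what the lower row is: "Precision of estimated incidence of stroke for different levels of incidence, and confidence intervals on effect sizes for quantitative measures". No formula, standard deviation or group structure is given for it.

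The analysis text after the table plans between-group work on continuous outcomes: "Comparison of follow-up and outcome data between treatment groups, cohorts, and regions will be made using linear (for continuous outcomes"). It does not refer back to the lower row.

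**The concern.** An effect size for a quantitative measure is ordinarily a difference between groups in standard-deviation units, so its precision depends on how many patients are in each group. The row gives only one n per column. In the total column that n is the entire registry, which leaves no second group to compare it with.

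This is the article's only precision figure for quantitative measures. If the total-column value assumes more patients than the registry will hold, a reader who relies on it will expect tighter intervals than any two-group comparison inside the UK data can give.

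**Working it through.** **Inputs.** n = 417, 833 and 4,582 from the column headings; 95% confidence, so z = 1.96; standard deviation 1, because the row is in effect-size units. Check of the total: 417 + 5 × 833 = 417 + 4,165 = 4,582.

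**Step 1. How the upper block uses n.** The single-sample half-width 1.96·sqrt(p(1−p)/n) at p = 2.5% gives 1.50 / 1.06 / 0.45 percentage points, printed as ±1.5 / ±1.1 / ±0.5. At p = 50% it gives 4.80 / 3.40 / 1.45, printed as ±4.8 / ±3.4 / ±1.4. All 21 cells reproduce. Here n is the number of patients in one sample.

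**Step 2. Which formula gives 0.14 / 0.10 / 0.04.**

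| Reading | 417 | 833 | 4,582 | Matches all three? |
|---|---|---|---|---|
| Two groups of n each, half-width, 1.96·sqrt(2/n) | 0.1357 | 0.0960 | 0.0409 | yes |
| Two groups of n each, full width | 0.27 | 0.19 | 0.08 | no |
| Column n split into two halves, half-width, 1.96·sqrt(4/n) | 0.192 | 0.136 | 0.058 | no |
| One mean, half-width, 1.96/sqrt(n) | 0.096 | 0.068 | 0.029 | no |
| One mean, full width | 0.192 | 0.136 | 0.058 | no |

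Among these ordinary 95% interval readings, only the first fits. It makes n a per-group size in the lower row, although the same columns are single-sample sizes in the upper block.

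**Step 3. What that reading means, column by column.**
- 833: one prospective cohort against another, 1.96·sqrt(2/833) = 0.096. The printed 0.10 is right.
- 417: there is no second retrospective group of 417. Against one prospective cohort, 1.96·sqrt(1/417 + 1/833) = 0.118, so the printed 0.14 is somewhat wider than needed.
- 4,582: two groups of this size would be 2 × 4,582 = 9,164 patients, twice the registry.

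**Step 4. What 4,582 patients can give in a two-group comparison**, using 1.96·sqrt(1/(4,582·s) + 1/(4,582·(1−s))) for a share s in one group:

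| Split | Half-width |
|---|---|
| 50/50 | 0.058 |
| 60/40 | 0.059 |
| 70/30 | 0.063 |
| 80/20 | 0.072 |
| 90/10 | 0.097 |

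The best case exceeds the value behind the printed figure by 0.0579/0.0409 = 1.41, that is sqrt(2).

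**Step 5. Could rounding explain it?** A printed 0.04 covers 0.035 to 0.045. With two equal groups the total needed is 4·(1.96/h)², about 12,540 at h = 0.035 and 7,590 at h = 0.045. The whole range exceeds 4,582.

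**The case against.** **The formula is inferred, and others fit.** This stands as a caution. A one-sample effect detectable with 80% power, (1.96 + 0.84)/sqrt(n), gives 0.137 / 0.097 / 0.041 and needs no second group. But the row is headed as a 95% confidence interval, so on that reading the label would be wrong instead. A within-patient change scaled by the baseline standard deviation has half-width 1.96·sqrt(2(1−r)/n), where r is the correlation between the two measurements. It coincides with the two-group formula at r = 0. For the first cell to print as 0.14, 0.1357·sqrt(1−r) must be at least 0.135, so r can be no more than about 0.01. That is implausible for repeated measurements on the same patients.

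**A reader might infer that the registry needs 9,164 patients, or that the row overstates precision throughout.** The article does not support either. The 9,164 is conditional on the inferred formula, and rounding widens it to the range in Step 5. Only the total cell is too favourable: the 833 cell is right for cohort against cohort, and the 417 cell errs on the cautious side. If a single mean was meant, 0.04 would understate the precision, since the half-width is 0.029.

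**A reader might also infer that the article promises ±0.04 for its treatment-group or region comparisons.** It does not say so. The text introduces Table 1 for stroke incidence, and the modelling paragraph does not cite the row.

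**Little rests on the row.** This is right and limits the severity. No sample size is derived from it and no test or decision rule uses it. The UK sizes are also close to one-twelfth of the global 5,000, 10,000 and 55,000 (417, 833 and 4,583), which suggests that they follow the global design. The missing ± signs may come from how the table was extracted, so they carry little weight.

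**A condensed article may leave the derivation to the full protocol.** The absence of a formula is therefore not the complaint. The complaint is a printed value that its own column size does not support.

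**Conclusion.** The point holds for one cell. On the only ordinary 95% interval reading that reproduces the row, the columns change from single-sample sizes in the incidence rows to per-group sizes in the effect-size row. The total-column 0.04 then cannot be achieved within a registry of 4,582. The best two-group half-width is ±0.058, about 1.4 times wider, and it grows with imbalance (±0.072 at 80/20).

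This rests on the inferred formula, on effect sizes in units of a common standard deviation, and on independent patients with no allowance for clustering by practice. That the total cell is wrong is less dependent on the formula: a single mean from 4,582 patients gives ±0.029 and the best two-group contrast ±0.058, and neither rounds to 0.04.

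The headings also call the values widths when they are half-widths. That is harmless where ± signs appear and ambiguous in the lower row.

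Severity is low to moderate. A stated precision figure needs correcting; the design, the sample size and the planned analyses are unaffected.

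**What to change.** State which comparison the effect-size row describes and restate it as 95% half-widths, with ± signs, in standard-deviation units:

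- 417 retrospective patients against one cohort of 833: ±0.12
- one cohort of 833 against another: ±0.10
- all 4,582 split 50/50: ±0.06; split 80/20: ±0.07

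If precision of a single mean was intended, replace the row with ±0.10 / ±0.07 / ±0.03 and amend the caption, which now refers to effect sizes. If another formula was used, state it and relabel the row to match.

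In either case, label the values in both blocks as half-widths and say whether the column size is a total or a per-group number.

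The cost is one table row, its headings and possibly the caption. The total-column figure becomes less favourable if a between-group comparison was meant, and more favourable if a single mean was meant. Nothing in recruitment or analysis changes.

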	**Width of 95% confidence interval**		
**Expected incidence of stroke**	**Sample size of retrospective patients: 417**	**Cohort size of prospective patients: 833**	**Total sample size of 4,582**
2.5%	±1.5%	±1.1%	±0.5%
5%	±2.1%	±1.5%	±0.6%
10%	±2.9%	±2.0%	±0.9%
20%	±3.8%	±2.7%	±1.2%
30%	±4.4%	±3.1%	±1.3%
40%	±4.7%	±3.3%	±1.4%
50%	±4.8%	±3.4%	±1.4%
Width of 95% confidence interval			
Sample size of retrospective patients: 417		Cohort size of prospective patients: 833	Total sample size of 4,582
0.14		0.10	0.04

An interim analysis will be done at the UK level for the baseline data in each cohort and after all patients in each of the first four cohorts have completed the study. For a full analysis, baseline data, follow-up data, and study endpoint data will be summarised overall and by treatment groups, cohort, and region. Summaries of categorical data will be presented as frequency counts, percentages, and 95% confidence intervals. Continuous data will be presented as means (standard deviations), medians (with 95% confidence intervals), interquartile ranges, minimum, maximum, and number of patients.

Comparison of follow-up and outcome data between treatment groups, cohorts, and regions will be made using linear (for continuous outcomes) or non-linear (for categorical outcomes) mixed modelling with practice included as a random effect. Association between outcome variables and baseline data will be explored using the same method. For continuous data, normality of residuals will be tested using the Kolmogorov–Smirnov test and transformation or bootstrapping will be implemented where required. Time-to-event analysis will use Kaplan–Meier and Cox regression analyses to summarise and explore the association with baseline and other pertinent data. Comparison of CHADS_2_, CHA_2_DS_2_VASc, and HAS-BLED risk measures will be compared on the basis of receiver-operating characteristic curve analyses. The baseline characteristics of the patients – who have been classified as at risk of stroke according to physician-perceived risk factors or combinations of factors – will be reported.

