**Methods/design:**

GARFIELD is an observational, international registry of newly diagnosed AF patients with at least one additional investigator-defined risk factor for stroke. The aim is to enrol 55,000 patients at more than 1000 centres in 50 countries worldwide. Enrolment will take place in five independent, sequential, prospective cohorts; the first cohort includes a retrospective validation cohort. Each cohort will be followed up for 2 years. The UK stands to be a significant contributor to GARFIELD, aiming to enrol 4,582 patients, and reflecting the care environment in which patients with AF are managed. The UK protocol will also focus on better understanding the validity of the two main stroke risk scores (CHADS_2_ and CHA_2_DS_2_VAS_C_) and the HAS-BLED bleeding risk score, in the context of a diverse patient population.

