## Background

Atrial fibrillation (AF) is the most common clinically significant arrhythmia in the adult population; it is an independent risk factor for stroke and mortality. People with AF have a fivefold increased risk of stroke and a twofold increased risk of death [1]. Prevalence of AF increases throughout life, affecting less than 1% of individuals under 60 years, approximately 4% of individuals over 60 years, and up to 10% of over those aged 80 years [2,3].

The estimated diagnosed prevalence of AF in the UK is around 1.4% [4,5], and more than 46,000 new cases of AF are diagnosed every year [6]. About 15% of all strokes are caused by AF, and 12,500 strokes each year in England are thought to be directly attributable to AF [7]. Furthermore, AF-related strokes are more serious: they are more likely to be fatal than strokes in patients without this arrhythmia; among patients who survive, these strokes cause more disability with less likelihood of independent recovery [8]. For example, findings from the Framingham study indicate that mortality is increased 1.84-fold in strokes in people with AF compared to those in sinus rhythm, and recurrence is more frequent [9]. The Copenhagen stroke study found that patients with AF require longer hospital stays (50 days versus 40 days, P < 0.001) and a lower discharge rate to their own homes (odds ratio 1.7; 95% confidence interval [CI] 0.44 to 0.85) with poorer neurological and functional outcomes [8]. Further, data from the European community stroke project show that AF increased by 50% the probability of remaining disabled (odds ratio 1.43; 95% CI 1.13 to 1.80) or handicapped (odds ratio 1.51; 95% CI 1.13 to 2.02) [10].

Management of AF requires either a rate-control strategy to slow the ventricular rate or a rhythm-control strategy in an attempt to maintain sinus rhythm. Regardless of whether the rate-control or the rhythm-control strategy is pursued, antithrombotic therapy for prevention of stroke and thromboembolism is a fundamental management tool.

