**Figure 1 F1:**
[figure not shown]
**NICE stroke risk stratification and thromboprophylaxis algorithm [**[15]**].** Reproduced with permission.

The prevalence of AF in the UK is increasing, probably due to the ageing population and improved survival from conditions predisposing to AF, including, for example, myocardial infarction. A large population-based study of the epidemiology and treatment of AF in the UK found prevalence of diagnosed AF rose steadily (0.84% in men in 1994 compared with 1.49% in 2003, compared with 0.83% and 1.29%, respectively, in women) [4]. The number and proportion of AF patients in the UK prescribed antithrombotic therapy has progressively increased over time [4,16]. An analysis of national data from 1994 to 2003 found under one-half of all AF patients received any antithrombotic treatment in 1994 but around 80% received some sort of stroke prevention in 2003 [4]. Also, treatment of AF with oral anticoagulants more than doubled from 1994 to 2003 in men (25% to 53%) and has increased significantly women (32% to 40%) [4]. However, the use of anticoagulants remains inappropriate [4,17] and the NICE 2006 costing report estimated that 46% of patients who should be on warfarin are not receiving it [18]. There is also evidence to suggest underuse of anticoagulation in the elderly; for example, in one study elderly patients (age >85 years) were less likely to initiate warfarin (relative rate 0.16, 95% CI 0.15 to 0.18) and more likely to start aspirin (relative rate 1.66, 95% CI 1.47 to 1.88) compared with patients aged 40–64 years [17].

Much of the UK evidence is based on retrospective cross-sectional studies and was derived from prevalence data. As such, there is limited evidence on persistence of treatment with antithrombotic therapy and it has been indicated that only 60% of patients prescribed warfarin continue for at least 2 years [17]. Also, much of the available evidence relates to AF management prior to the publication of the NICE guidelines in 2006. It is not clear how well clinicians adhere to these guidelines and what impact this has had. There is an absence of contemporary longitudinal data on the clinical management of AF in the UK, including the key therapeutic area of antithrombotic therapy, persistence of therapy, and related clinical outcomes.

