### Study aims

The key aims of the GARFIELD registry are to determine the real-life treatment patterns and clinical outcomes of newly diagnosed patients with non-valvular AF with at least one additional risk factor for stroke.

In accordance with the global objectives, the study will assess the rate of stroke and systemic embolisation, and assess the outcome of these events with specific reference to:

• The incidence and characteristics of bleeding complications (e.g. location and severity, classified as major, clinically relevant non-major, and minor);

• Therapy persistence, including discontinuation, interruption, and changes of therapy regimen;

• For patients on VKAs, fluctuations in the INR over time.

The UK protocol has additional objectives that will inform the management on AF. GARFIELD in the UK seeks to evaluate the performance of the novel stroke risk score CHA_2_DS_2_-VASc in comparison with CHADS_2_ in predicting stroke risk in the UK study population. Likewise it will evaluate the effectiveness of the bleeding risk score HAS-BLED in predicting bleeding risk within the UK study population. In addition, the study will determine the clinician and patient factors associated with the decision to anticoagulate patients. Another unique objective of the UK study is to determine any variations in levels of anticoagulation associated with ethnicity. Furthermore, the study will determine where patients are principally diagnosed with AF and assess the role of primary care in the management of AF in the UK.

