#### Prospective cohorts

The eligibility criteria for the prospective cohorts are: patients aged 18 years or older with a diagnosis of non-valvular AF within the past 6 weeks and at least one additional risk factor for stroke [19].

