### Collection of baseline and follow-up data

Data collected at baseline include: demographics (e.g. ethnicity, sex, date of birth); body mass index; vital signs at diagnosis; AF symptoms; type of AF (new, paroxysmal, persistent, permanent); method and site of diagnosis; treatment strategy initiated at diagnosis; antithrombotic therapy; treatment decision (patient and physician factors); and medical history (cardiovascular, medical, bleeding).

Follow-up data include clinical events (stroke/TIA, peripheral embolism, acute coronary syndrome) and outcome of event; AF-related medical consultation and/or hospitalisation and outcome; AF treatment change; change in antithrombotic therapy (discontinuation, duration on therapy, reasons for discontinuation); bleeding events (classified as major, clinical relevant non-major, and minor); bleeding location of treatment (e.g. Accident and Emergency, GP practice); outcome of bleeding (recovered, permanently disabled, fatal); bleeding healthcare utilisation (hospitalisation, Accident and Emergency, physician, etc.); medical history update; mortality, including sudden cardiac death and non-cardiovascular death; and INR records in relation to therapeutic range, and location of INR monitoring.

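### Kaplan–Meier is the only named time-to-event summary; for outcomes that death precludes, cumulative incidence with death as a competing event fits the registry's aim better

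*Protocol article*

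**What the plan says.** In Sample size and data analysis, the protocol article says: "Time-to-event analysis will use Kaplan–Meier and Cox regression analyses to summarise and explore the association with baseline and other pertinent data". It does not list the outcomes this covers, say what happens to patients who die before the event, or name a competing-risk method.

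The same section plans a second kind of summary: "Summaries of categorical data will be presented as frequency counts, percentages, and 95% confidence intervals". Table 1 sizes the study on stroke incidence as a percentage of patients.

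Under Study aims, absolute frequency is an explicit target: "the study will assess the rate of stroke and systemic embolisation". Clinical outcomes and data quality lists stroke, TIA, systemic embolism, bleeding and therapy persistence, with mortality as a separate outcome. Death is captured in follow-up as "mortality, including sudden cardiac death and non-cardiovascular death". The abstract gives the horizon: "Each cohort will be followed up for 2 years".

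On mortality, the Background offers only a relative statement: "People with AF have a fivefold increased risk of stroke and a twofold increased risk of death". No 2-year death rate is given.

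**The concern.** A patient who dies without a stroke can no longer have one. Kaplan–Meier with that death censored treats the patient as still able to have the event later, at the same rate as survivors. One minus Kaplan–Meier then estimates the risk in a population from which death has been removed. A registry that sets out to describe real-life outcomes wants the proportion of newly diagnosed patients who actually have the event within 2 years, which is the cumulative incidence.

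The plan could also report two different 2-year figures for one outcome. With complete follow-up, the crude percentage equals the cumulative incidence, and the Kaplan–Meier figure would be higher. Nothing in the article tells the reader which one is the registry's incidence.

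**Working it through.** **Step 1. What Table 1 measures.** The binomial half-width 1.96 × √(p(1−p)/n) reproduces all 21 stroke cells to the printed decimal. At p = 10% it gives 2.88, 2.04 and 0.87 points for n = 417, 833 and 4,582, against the printed ±2.9, ±2.0 and ±0.9. The total is 417 + 5 × 833 = 4,582. Table 1 therefore treats incidence as a simple proportion, with patients who die event-free counted as non-events.

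**Step 2. Direction.** Both estimators add up events over time. Kaplan–Meier weights each event by survival from the event alone. Aalen–Johansen weights it by the probability of being alive and event-free, which is never larger. With deaths censored, one minus Kaplan–Meier therefore cannot fall below the cumulative incidence. This needs no assumption about hazards.

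**Step 3. Size.** Assumptions: constant, independent hazards over 2 years, l for the event and m for death. The 2-year mortality D is not in the article and is varied from 5% to 30%.

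- Kaplan–Meier risk: R = 1 − exp(−2l)
- Mortality: D = 1 − exp(−2m)
- Cumulative incidence: C = l/(l+m) × (1 − exp(−2(l+m))), where exp(−2(l+m)) = (1−R)(1−D)

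Example with R = 5% and D = 10%: l = −ln(0.95)/2 = 0.02565 and m = −ln(0.90)/2 = 0.05268. So C = 0.02565/0.07833 × (1 − 0.95 × 0.90) = 0.3274 × 0.145 = 4.75%. With D = 20% the same steps give C = 4.49%.

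**Step 4. Table 1 levels taken as the true cumulative incidence.** Solving for l gives the figure that death-censored Kaplan–Meier would show (excess in points in brackets):

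| True 2-year incidence | D = 5% | D = 10% | D = 20% | D = 30% | Table 1 half-width, per cohort / overall |
|---|---|---|---|---|---|
| 5% | 5.13 (0.13) | 5.27 (0.27) | 5.57 (0.57) | 5.93 (0.93) | ±1.5 / ±0.6 |
| 10% | 10.25 (0.25) | 10.53 (0.53) | 11.13 (1.13) | 11.84 (1.84) | ±2.0 / ±0.9 |
| 20% | 20.50 (0.50) | 21.03 (1.03) | 22.21 (2.21) | 23.59 (3.59) | ±2.7 / ±1.2 |
| 40% | 40.94 (0.94) | 41.94 (1.94) | 44.15 (4.15) | 46.69 (6.69) | see below |

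The relative excess is about 2.5% at 5% mortality, 5% at 10%, 11% at 20% and 17–19% at 30%.

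The 40% row is the discontinuation level implied by the Background's remark that "only 60% of patients prescribed warfarin continue for at least 2 years" (100 − 60 = 40). No Table 1 half-width is set against it, because only treated patients can discontinue and their number is not given.

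**The case against.** The strongest reply is that the sentence never says deaths are censored, Kaplan–Meier is correct for all-cause mortality (itself an outcome), and a condensed article may leave the handling of death to a full protocol or analysis plan that is not shown. Part of this stands: censoring at death is inferred from ordinary use of the method. But the article does more than stay silent. It names the estimator, and most of its listed events are ones that death precludes.

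A second reply is that percentages are planned too, so Kaplan–Meier is not the sole incidence summary. That is right, and it limits the harm. It does not settle which figure is the registry's incidence, and a crude percentage equals the cumulative incidence only when follow-up is complete.

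A third concerns persistence. Stopping treatment while alive is a legitimate target, and death-censored estimation can serve it. That also stands, so for persistence the request is to name the target.

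Three stronger readings are tempting but unsupported:

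- A reader might infer that comparisons between treatment groups, cohorts and regions are distorted. The article assigns those to mixed models with a random practice effect. Cox regression with deaths censored remains valid for cause-specific hazards.
- A reader might set the excess for discontinuation against Table 1's ±1.4 for 40% at n = 4,582, and argue that it stands out even if every patient were treated. That runs backwards, because treating everyone gives the narrowest interval. If half were treated (assumed, n = 2,291), the half-width is 1.96 × √(0.4 × 0.6/2,291) ≈ 2.0 points, and the 1.94-point excess at 10% mortality lies just inside it.
- A reader might take an elderly population with high mortality as given. Eligibility covers "patients aged 18 years or older with a diagnosis of non-valvular AF within the past 6 weeks", with no age distribution. An older population is a fair inference from the Background's account of AF and age, but the death rate remains an assumption.

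**Conclusion.** The point holds in limited form. For absolute 2-year risks of stroke, TIA, systemic embolism and bleeding, the named estimator in its ordinary use overstates the real-life figure, and a better one needs no new data.

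For a 5% stroke incidence the excess is 0.13 to 0.57 points at 5% to 20% mortality. That is within Table 1's overall ±0.6 and well within the per-cohort ±1.5. Only at 30% mortality (0.93 points) does it pass the overall figure. For incidences of 10% and 20%, the excess passes the overall half-width at 20% mortality (1.13 against ±0.9; 2.21 against ±1.2) but stays within the per-cohort one.

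The direction is certain if deaths are censored. The size rests on the assumed mortality and on constant, independent hazards. The mixed models, the Cox models, Kaplan–Meier for all-cause mortality and the sample size are unaffected.

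**What to change.** Amend the time-to-event sentence as follows:

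- For outcomes other than death, estimate absolute risks with the Aalen–Johansen cumulative incidence, with death before the event as the competing event.
- Keep Kaplan–Meier for all-cause mortality.
- Keep the Cox models and label their hazard ratios cause-specific.
- For therapy persistence, state whether the target is discontinuation with death as a competing event or persistence while alive. Report the cumulative incidence at least alongside.

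The cost is wording and a little extra analysis, since mortality is already recorded. Where Kaplan–Meier figures would have been reported, the incidences become slightly lower. Sample size and Table 1 stay as they are.
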